## Abstract

**Background:**

Pulmonary rehabilitation is an effective therapeutic intervention for people with chronic respiratory disease. However, fewer than 5% of eligible individuals receive pulmonary rehabilitation on an annual basis, largely due to limited availability of services and difficulties associated with travel and transport. The Rehabilitation Exercise At Home (REAcH) study is an assessor-blinded, multi-centre, randomised controlled equivalence trial designed to compare the efficacy of home-based telerehabilitation and traditional centre-based pulmonary rehabilitation in people with chronic respiratory disease.

**Methods:**

Participants will undertake an 8-week group-based pulmonary rehabilitation program of twice-weekly supervised exercise training, either in-person at a centre-based pulmonary rehabilitation program or remotely from their home via the Internet. Supervised exercise training sessions will include 30 min of aerobic exercise (cycle and/or walking training). Individualised education and self-management training will be delivered. All participants will be prescribed a home exercise program of walking and strengthening activities.

Outcomes will be assessed by a blinded assessor at baseline, after completion of the intervention, and 12-months post intervention. The primary outcome is change in dyspnea score as measured by the Chronic Respiratory Questionnaire – dyspnea domain (CRQ-D). Secondary outcomes will evaluate the efficacy of telerehabilitation on 6-min walk distance, endurance cycle time during a constant work rate test, physical activity and quality of life. Adherence to pulmonary rehabilitation between the two models will be compared. A full economic analysis from a societal perspective will be undertaken to determine the cost-effectiveness of telerehabilitation compared to centre-based pulmonary rehabilitation.

**Discussion:**

Alternative models of pulmonary rehabilitation are required to improve both equity of access and patient-related outcomes. This trial will establish whether telerehabilitation can achieve equivalent improvement in outcomes compared to traditional centre-based pulmonary rehabilitation. If efficacious and cost-effective, the proposed telerehabilitation model is designed to be rapidly deployed into clinical practice.

**Trial registration:**

Clinical trial registered with the Australian and New Zealand Clinical Trials Register at (ACTRN12616000360415). Registered 21 March 2016.

## Background

Chronic respiratory diseases, including chronic obstructive pulmonary disease (COPD), interstitial lung diseases (ILD), bronchiectasis and chronic asthma, contribute 7% to the global burden of disease [1]. Chronic respiratory diseases are the third leading cause of death worldwide, and account for 10% of all disability adjusted life years lost due to disability alone [2]. This level of disability is second only to that of cardiovascular disease, including stroke [2]. People with chronic respiratory disease experience repeated need for hospitalisation, reduced quality of life and life expectancy, poor exercise tolerance and physical functioning, and increased incidence of anxiety and depression [3]**.**

Pulmonary rehabilitation is a proven, effective strategy to achieve clinically important gains in exercise and functional capacity, symptoms and quality of life [4] across a variety of chronic respiratory diseases, including COPD [5], bronchiectasis [6], ILD [7] and asthma [8]. Participation in pulmonary rehabilitation also reduces hospitalisation due to acute exacerbations of respiratory disease [9] as well as overall healthcare utilisation [10]. Pulmonary rehabilitation is a recommended treatment strategy for individuals with a chronic respiratory disease in clinical guidelines across the world [4].

Despite compelling evidence for the benefit of pulmonary rehabilitation, only a very small percentage of eligible people ever attend a program [11]. There are well established barriers to uptake and participation in traditional centre-based pulmonary rehabilitation programs, both in the hospital and in the community, relating to referral practices, travel, transport, disability and lack of program staffing [12, 13]. Such barriers disproportionately compromise access to programs for patients in rural and regional locations [14]. In light of such obstacles, alternative modes of delivering pulmonary rehabilitation, in addition to traditional centre-based programs, are required to improve both equity of access and patient-related outcomes for people with chronic respiratory diseases and have been identified as a research priority [15].

Home-based models of pulmonary rehabilitation have been proposed to increase the availability and accessibility of pulmonary rehabilitation services to patients [16–20]. Recent work has demonstrated that home-based pulmonary rehabilitation achieves equivalent clinical outcomes to centre-based pulmonary rehabilitation [20]. However, a disadvantage of such programs is the lack of supervised exercise training. Advances in Internet technology and accessibility have made it possible for people to receive specialist medical care and therapeutic interventions straight to their home. Telerehabilitation is the use of information and communication technologies to provide clinical rehabilitation services from a distance [21]. Using the Internet, rehabilitation can be delivered directly to the patient’s location, regardless of physical proximity to a rehabilitation centre. Whilst telerehabilitation technology has existed for many years, the clinical efficacy of this model is not clear.

Preliminary studies have described the use of telerehabilitation in COPD, using a variety of program models. These studies suggest that telerehabilitation in COPD is safe, with no adverse events reported [22–28]. However, most existing trials have a number of important limitations, including: the requirement for participants to attend a health facility in order to access the telerehabilition service [22]; the use of bespoke, proprietary or poorly defined equipment to deliver telerehabilitation and monitor vital signs [23–25, 27]; failing to include supervised exercise training in the telerehabilitation model [23, 24, 27], and limiting the scope of application to individuals with COPD. These factors limit the clinical utility of previous telerehabilitation programs through restricted access [12], and omission of an essential component of pulmonary rehabilitation [4]. We have previously demonstrated the feasibility of a telerehabilitation model that delivers all the essential components of pulmonary rehabilitation into the home of people with COPD [28]. By using readily available equipment such as an exercise bike and a tablet computer it is possible for people to undertake a supervised exercise training program in their own home. However, to date, a comparison of the outcomes and costs of telerehabilitation to centre-based pulmonary rehabilitation has only been undertaken in the maintenance period post-rehabilitation [29]. A telerehabilitation model that allows all the essential components of pulmonary rehabilitation, specifically supervised exercise training and self-management education, to be delivered at home, using readily available equipment, with proven clinical outcomes and comparable costs, has the potential to dramatically change the uptake and accessibility of pulmonary rehabilitation for all patients with a chronic respiratory disease.

Analysing the cost of telerehabilitation is critical to determine the economic viability of implementing such a model into clinical practice. To date, there is a lack of evidence to support the cost-effectiveness of telerehabilitation, despite apparent clinical benefits in a range of health conditions [21]. A comprehensive assessment of the economic value of telerehabilitation needs to include both costs to the healthcare system, including the initial costs of equipment and its transport [30], together with costs to the patient [31]. Telerehabilitation has the potential to overcome many known barriers to pulmonary rehabilitation participation and, if cost-effective, could be a relevant treatment alternative across all chronic respiratory diseases where rehabilitation is an accepted therapeutic intervention.

This paper describes the protocol for the Rehabilitation Exercise At Home (REAcH) trial – a study of telerehabilitation in chronic respiratory disease. The aims of the study are to compare the: 1) clinical outcomes of telerehabilitation and traditional centre-based pulmonary rehabilitation for people with a chronic respiratory disease; 2) costs of telerehabilitation and centre-based pulmonary rehabilitation. We hypothesise that the clinical effects on symptoms, exercise capacity, and health-related quality of life (HRQoL) will be equivalent between pulmonary rehabilitation models; that the proportion of participants who complete pulmonary rehabilitation will be greater in the telerehabilitation group; and, that telerehabilitation, delivered using our low-cost model, will provide a cost-effective alternative to centre-based pulmonary rehabilitation (from a societal perspective) for people with chronic respiratory disease.

## Methods

### Design

A randomised, controlled, assessor-blinded equivalence trial with an embedded economic evaluation will be conducted at two centres in metropolitan Melbourne (Alfred Health and Austin Health), and one regional centre (Wimmera Health Care Group, Horsham), Australia. Both regional and metropolitan sites have been included to increase the external validity of our model. The study was approved by the Human Research Ethics Committee at Alfred Health for all sites, and local governance approvals obtained from all participating sites (Austin Health, Wimmera Health Care Group and West Wimmera Health Service). The trial was registered at anzctr.org.au (ACTRN12616000360415) on March 21, 2016.

### Participants

Potential participants will be referred to pulmonary rehabilitation at the established centre-based programs of the participating sites, or those individuals admitted to hospital with an exacerbation of their respiratory disease. To be eligible for inclusion participants will: 1) have a primary diagnosis of a chronic lung disease; 2) be aged ≥40 years; and 3) be able to read and speak English. Potential participants will be excluded if they have: 1) a primary diagnosis of pulmonary hypertension or lung cancer, as rehabilitation is not yet a well established treatment for these diagnoses; 2) attended pulmonary rehabilitation within the previous 18 months and had no hospitalisations for a respiratory cause since rehabilitation completion, as these patients may not achieve further benefits; 3) oxygen desaturation resulting in cessation of cardiopulmonary exercise testing (e.g. SpO_2_ < 80% during exercise on cycle ergometer), to ensure safety of unsupervised training; 4) unstable or brittle asthma with a hospital admission or emergency department presentation within the preceding 3 months, to ensure safety of unsupervised training; 5) co-morbidities which preclude exercise training, such as neurological or musculoskeletal impairment; or 6) are unable to follow verbal instructions, suffer from cognitive impairment, or have language difficulties. Eligible participants will be provided with written and verbal information about the study from a clinician and/or a researcher. All participants will provide written consent. Trial participation will have no effect on routine management of their respiratory condition or any other healthcare requirements.

### Recruitment and randomisation

Participants will be randomly allocated (1:1) to traditional centre-based pulmonary rehabilitation or telerehabilitation. A computer-generated, block randomisation scheme will be used with stratification for (i) recruitment in stable state vs post hospitalisation for respiratory exacerbation; (ii) site of recruitment; and (iii) diagnosis of ILD vs other diagnoses. Sequence generation will be performed by an individual who is independent of the research team and randomisation will occur using an online database. The randomisation sequence will be concealed from investigators. Participants will be allocated to groups after completion of baseline assessment. Given the nature of the intervention (exercise training) participants will not be blinded to the intervention, however all outcomes will be measured by an independent assessor blind to group allocation. The flow of participants through the study will be reported according to the recommendations of the Consolidated Standard of Reporting Trials (CONSORT) [32].

### Interventions

#### Centre-based pulmonary rehabilitation

Participants will undergo a standard outpatient pulmonary rehabilitation program at the centre where they were recruited, according to Australian best-practice guidelines [33]. This involves 8 weeks of twice-weekly supervised sessions in groups of 8–12 participants, supervised by a health professional experienced in the delivery of pulmonary rehabilitation (eg. physiotherapist, exercise physiologist) and appropriately qualified assistants (eg. allied health assistant, nurse). Participants will undertake at least 30 min of lower limb aerobic training each session, which may be completed in shorter intervals if continuous training is limited by symptoms (eg. 3 × 10 minutes or 2 × 15 minutes). A combination of cycling and walking will be used, with the initial walking exercise intensity set at 70–80% of the speed walked on a 6-min walk test and cycle ergometer intensity set at the work rate equivalent to 60% of the peak oxygen uptake (VO_2_) on a cardiopulmonary exercise test (CPET) [34]. Intensity of both cycle and walking training will be progressed each week with the aim of maintaining Borg dyspnoea scores of 3–4.Cycle training will be progressed by 5–10% of the initial workload [35] and walking speed by 0.25 or 0.5 km/hour depending on initial training speed (< 3 km/hour or ≥ 3 km/hour respectively). Resistance training will utilise functional activities such as sit-to-stand from a chair and upper limb weights. Initial weights will be prescribed as tolerated, to achieve 8–12 repetitions for 3 sets of each exercise. Once the participant achieves 3 sets of 12 repetitions then the weight will be increased. Participants will be encouraged to perform an additional 3 unsupervised sessions each week, which will be documented in a home diary that is reviewed weekly by the supervising physiotherapist. A record of sessions attended by each participant will be maintained. Exercise training will be standardised across all sites with the use of a protocol for prescription and progression.

#### Telerehabilitation

Remotely supervised telerehabilitation at home will be conducted twice a week for 8 weeks, in groups of 4–6 participants at a time, supervised by an experienced physiotherapist. Exercise training will comprise 30 min of lower limb aerobic training and individualised strength training exercises. Participants will undertake a total of 30 min of cycle training, in two or more bouts, in each telerehabilitation session. Cycle ergometer intensity for telerehabilitation participants will be set with the same parameters as for centre-based participants, that is, at the work rate equivalent to 60% of the peak oxygen uptake (VO_2_) on a cardiopulmonary exercise test (CPET) [34]. Intensity of cycle training will be progressed each week by 5–10% of the initial workload as tolerated [35], based on patient symptoms. Resistance training for the arms and legs will utilise equipment readily available in the home environment (e.g. sit to stand from a standard height chair, bags of rice for upper limb weights). Resistance training will be initially prescribed as tolerated, to achieve 8–12 repetitions for 3 sets of each exercise. Similar to the centre-based group, telerehabilitation participants will also be encouraged to perform an additional 3 unsupervised sessions each week, which will be documented in a home diary that is reviewed weekly by the supervising physiotherapist.

The telerehabilitation set-up will be based on our successfully piloted model [28] using readily available equipment. It will comprise a step-through exercise bike to maximise safety (Bodyworkx A915); a tablet computer (iPad – for relative ease of use and limited need to negotiate menu functions) fixed to a stand for videoconferencing; and a pulse oximeter (Nonin Palmsat 2500A; Nonin Medical Inc., Plymouth, Minnesota, USA) to monitor SpO_2_ and heart rate during training and at rest. The oximeter will not use Bluetooth but will be positioned such that the display is visible to the supervising physiotherapist throughout the session. Videoconferencing will be via Zoom videoconferencing software (San Jose, California, USA) that enables all participants to see and speak to each other. To ensure safety and understanding of equipment operation and the exercise program, the initial training session and establishment of the home exercise program will occur during a home visit by a physiotherapist.

Fidelity of the exercise training intervention for both groups will be facilitated through regular staff training, audit of exercise prescription and progression, and assessment of participant engagement [36].

Disease-specific education and collaborative self-management training will be delivered to participants in both groups according to international guidelines [4]. To standardise provision of information, participants in both groups will receive self-management education resources from Lung Foundation Australia in the form of a printed book and brochure detailing the location of online resources [37]. These resources have been developed to enable people with chronic respiratory diseases to undertake the educational component of pulmonary rehabilitation at their convenience. Self-management education for all participants will include long-term exercise planning and, for patients with COPD or asthma, education regarding identifying and managing an acute exacerbation. Additional topics relating to self-care in chronic respiratory disease, such as airway clearance techniques and strategies for maintaining a healthy diet will also be addressed where participants identify a relevant health goal. After the 8-week rehabilitation program, all participants in both groups will be encouraged to continue with a regular exercise regimen. All participants will be offered the opportunity to join a supervised exercise maintenance program to promote ongoing exercise adherence, in line with national standards [33]. The proportion of each group that accept a referral and attend a program will be documented.

##### Outcome measures

Demographic details of age, gender, diagnosis, body mass index (BMI) and lung function will be collected at baseline. A maximal CPET using cycle ergometry with expired gas analysis will be completed as part of the baseline assessment to establish a work rate for an endurance cycle test (see secondary outcomes). Attendance rates at training sessions will be documented at the end of the intervention period and compared between the centre-based and telerehabilitation groups, with an a priori definition of pulmonary rehabilitation adherence (i.e. program completion) as undertaking a minimum of 70% of planned pulmonary rehabilitation sessions [38].

Participants will undertake assessment of clinical outcome measures at baseline, end intervention and after 12-months follow-up (see Fig. 1). The following measures will be recorded:

**Fig. 1 Fig1:**
[figure not shown]
Participant schedule. Legend: + = completed; − = not completed; 6MWT = six minute walk test; CPET = cardiopulmonary exercise test; ECT = endurance cycle test

##### Primary outcome

The Chronic Respiratory Disease Questionnaire (CRQ) is a disease specific measure of HRQoL for people with chronic respiratory disease [39]. The CRQ scores the domains of dyspnea, fatigue, mastery and emotional function. The primary outcome will be change in CRQ dyspnea domain (CRQ-D) from baseline to end intervention. The CRQ-D is a valid measure of HRQoL and is responsive to change with pulmonary rehabilitation in people with chronic respiratory diseases including COPD [40], bronchiectasis [41] and ILD [42].

##### Secondary outcomes

Exercise capacity will be measured using both the 6-min walk distance (6MWD) and endurance cycle time. The 6MWD will be measured using the 6-min walk test which is a validated measure of functional exercise capacity [43], and is responsive to change following pulmonary rehabilitation in people with chronic respiratory diseases [44, 45]. Two tests will be completed at each assessment time-point according to standard procedures and the best distance used for analysis [43]. Endurance cycle time will be measured during a constant work rate exercise test, performed at 75% of the peak work rate on the baseline CPET. Endurance cycle time is highly responsive to therapeutic interventions in people with chronic respiratory disease [46, 47].

The CRQ domains of fatigue, mastery and emotional function, reflecting HRQoL, will be reported as secondary outcomes. The SF-36v2, a validated generic quality of life measure will be used to derive a preference-based measure of utility, the SF-6D, for economic analyses [48].

Self-efficacy will be measured using the Pulmonary Rehabilitation Adapted Index of Self Efficacy (PRAISE) tool, a reliable and sensitive measure of self-efficacy for patients attending pulmonary rehabilitation [49].

Dyspnea will be measured using the Modified Medical Research Council scale [50].

Anxiety and depression will be evaluated using the Hospital Anxiety and Depression Scale [51]. Anxiety and depression are common comorbidities in people with chronic respiratory disease and can be ameliorated with pulmonary rehabilitation [4].

Physical activity levels will be measured objectively using a wrist-worn activity monitor over seven days (GeneActiv; ActivInsights Ltd., Kimbolton, Cambridgeshire, United Kingdom). The GeneActiv is a tri-axial accelerometer that is validated for the assessment of free-living activity in healthy people [52] and has been used to assess physical activity in people with chronic respiratory disease [53]. Data will be collected and stored as raw acceleration in g units (m/s^2^) for offline analysis. Time (minutes) per day spent in sedentary, light, moderate and vigorous physical activity will be reported.

### Economic evaluation

Economic evaluation will take a societal perspective [54]. Economic evaluation will incorporate costs for all stakeholders involved, including participants’ out-of-pocket costs associated with health care services, and the costs of health services, including intervention costs. To facilitate documentation of personal health care costs, participants will be contacted by telephone every month during the 12-month follow-up period to document self-reported health care utilisation and to encourage completion of the monthly diary. Individual-level data for outcomes of Quality-Adjusted Life Years (QALYs), CRQ-D scores and costs will be compared to assess the incremental impact of telerehabilitation compared to traditional centre-based pulmonary rehabilitation. To compare differences in costs with differences in QALYs the SF6D score, which determines an individual’s self-valuation of health state at a specific time-point and is generated from the SF36-v2, will be converted into QALYs [55]. In addition, a separate assessment of cost effectiveness will also be undertaken by comparing the change in CRQ-D scores from baseline to end rehabilitation to the incremental costs of the intervention.

Direct costs of telerehabilitation may be higher than those for centre-based pulmonary rehabilitation, due to capital expenditure for equipment, but these may be accompanied by savings in the form of averted expenditure on health service use. Thus we will also calculate the (internal) rate of monetary return from investing in the intervention, which compares the difference in costs of health service use associated with telerehabilitation and centre-based rehabilitation to initial outlay for infrastructure [30]. For this purpose, any savings from lowering health system costs will be assessed over a time horizon of 12-months [30]. Sensitivity analyses will capture variations in cost of establishing telerehabilitation in rural versus urban settings in Australia.

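### The rate of return sets health-service savings against infrastructure outlay and leaves out recurring delivery costs, which differ between arms, so it is biased in a direction the protocol cannot settle

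*Protocol article*

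**What the plan says.** The Economic evaluation section of the protocol article plans a QALY-based and a CRQ-D-based comparison with costs and then adds a rate of return on investing in telerehabilitation. That measure "compares the difference in costs of health service use associated with telerehabilitation and centre-based rehabilitation to initial outlay for infrastructure".

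The sentence before it says direct costs of telerehabilitation may be higher "due to capital expenditure for equipment, but these may be accompanied by savings in the form of averted expenditure on health service use". The sentence after it says that "any savings from lowering health system costs will be assessed over a time horizon of 12-months". The only sensitivity analyses named in the section concern the cost of setting up telerehabilitation in rural and urban settings.

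Earlier, the same section says the evaluation as a whole covers "the costs of health services, including intervention costs". The second cost-effectiveness analysis works by "comparing the change in CRQ-D scores from baseline to end rehabilitation to the incremental costs of the intervention".

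The Interventions section describes delivery:

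- **Telerehabilitation:** sessions run "in groups of 4–6 participants at a time, supervised by an experienced physiotherapist", and "the initial training session and establishment of the home exercise program will occur during a home visit by a physiotherapist".
- **Centre-based:** the programme is "8 weeks of twice-weekly supervised sessions in groups of 8–12 participants", led by a health professional together with assistants. Their number is not given.

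**The concern.** A return on investment should set the outlay against the net annual benefit of switching from one programme to the other. That benefit has two parts: the change in later health-service use, and the change in what it costs to run the programme. The stated definition names only the first. The text around it points the same way, since equipment is the only reason given for higher direct costs and the savings are described as averted health-service spending.

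Supervision, home visits and facility use are not infrastructure. They recur with every group or participant, and the two arms are designed differently on all of them. A return computed as stated could be positive while the switch loses money once running costs are counted, or negative while it gains. A health service deciding whether to invest would be a natural user of this figure. It could also point the other way from the cost-effectiveness results, which do carry intervention costs.

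**Working it through.** The article gives no rate of return, unit cost or outlay, so there is no figure to reproduce. Two things can be checked: how the omission acts on the return, and whether the documents fix its direction.

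**1. Effect on the return.** Per participant, let K be the infrastructure outlay, S the health-service saving over 12 months, and D the recurring delivery cost of telerehabilitation minus that of the centre. With one outlay and a single 12-month return:

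- as written: (S − K)/K
- net of delivery: (S − D − K)/K
- difference: D/K

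Illustration with assumed values K = 1000 and S = 1200, in arbitrary units. The return as written is (1200 − 1000)/1000 = +20%.

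| D | Return net of delivery |
|---|---|
| −200 | +40% |
| 0 | +20% |
| +200 | 0% |
| +400 | −20% |

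Both size and sign can change, and the sign of D decides the direction.

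**2. Inputs for D from the Interventions section.** Each arm has 8 weeks × 2 = 16 sessions. Group size is 8–12 at the centre and 4–6 for telerehabilitation (4/8 = 6/12 = 0.5). Telerehabilitation has one physiotherapist and one home visit for the initial session. The centre has one health professional plus assistants.

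Assumed, because not stated: a assistants per centre group, each costing a fraction w of the lead clinician; the home visit counted as one session, without travel.

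Staff-sessions per participant, for group size g:

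- Centre: 16(1 + aw)/g
- Telerehabilitation: 15/g + 1 if the visit replaces a group session, or 16/g + 1 if it is additional

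**3. Lead clinician only (a = 0).**

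- Centre: 16/12 to 16/8 = 1.33 to 2.00
- Telerehabilitation without the visit: 16/6 to 16/4 = 2.67 to 4.00
- Telerehabilitation with the visit: 15/6 + 1 to 15/4 + 1 = 3.50 to 4.75, or 16/6 + 1 to 16/4 + 1 = 3.67 to 5.00

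**4. With assistants, at mid-range group sizes (10 and 5).** Telerehabilitation is 15/5 + 1 = 4.0 or 16/5 + 1 = 4.2.

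| Assistants a | Relative cost w | Centre | Telerehabilitation minus centre |
|---|---|---|---|
| 0 | – | 1.60 | +2.4 to +2.6 |
| 1 | 1 | 3.20 | +0.8 to +1.0 |
| 1 | 0.6 | 2.56 | +1.44 to +1.64 |
| 2 | 1 | 4.80 | −0.8 to −0.6 |
| 2 | 0.6 | 3.52 | +0.48 to +0.68 |
| 3 | 0.6 | 4.48 | −0.48 to −0.28 |

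One equal-cost assistant cancels the group-size effect and leaves only the home visit. The staffing gap is zero when 16(1 + aw)/10 = 4.0, so aw = 1.5 (or aw = 1.625 against 4.2). In words, the gap closes when the assistants together cost about one and a half lead clinicians.

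Home-visit travel would raise D and the centre's facility cost would lower it. Neither is quantified in the article.

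**The case against.** **The wording may already cover it.** The section's opening includes intervention costs in the evaluation, so the cost difference in the rate of return could be read as including programme delivery. This reading is possible. However, that phrase describes the evaluation as a whole, while the rate-of-return text speaks of health-service use and explains it as averted spending. If the wider reading is meant, equipment could be counted twice, once as an intervention cost and once as outlay, so the definition would still need a clarifying clause.

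**An article condenses.** How cash flows are built can be left to a full economic plan, and the article cites a source for the method. This would answer a complaint about missing detail. Here, though, the article states what goes on each side of the comparison, and that statement is the problem.

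**The return is not shown to be overstated.** A reader might infer overstatement from the half-size groups and the home visit. The documents do not support that. The centre uses assistants, in the plural, and a facility, and the table above shows the staffing gap changing sign within plausible assumptions. This objection stands in full.

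**The measure is supplementary.** This also stands. The QALY and CRQ-D analyses include intervention costs and are not affected.

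**Conclusion.** The point holds as a bias of unknown direction in one supplementary measure. On its natural reading, the rate of return omits recurring delivery costs that the protocol's own design makes different between the arms. The error is D/K: the return is overstated if telerehabilitation costs more per participant to deliver, and understated if it costs less.

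Under the assumptions tried, the mid-range staffing difference runs from +2.6 to −0.8 staff-sessions per participant, before travel and facility costs. Converting this to money needs assistant numbers, unit costs and the outlay, none of which the article gives. A firm claim of overstatement, or of telerehabilitation being about twice as costly to supervise, would rest on counting the lead clinician alone.

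**What to change.** Redefine the cash flow in the rate of return as health-service savings minus the difference in recurring delivery cost per participant (telerehabilitation minus centre-based). That difference should cover:

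- clinician and assistant time at the actual group sizes
- the home visit and its travel
- equipment transport
- facility use

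Set this net flow against the infrastructure outlay, and count equipment once only, as outlay.

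The change is one of wording and formula. The intervention costs already planned for the cost-effectiveness analyses can supply the inputs. The price is that the reported return may become less favourable, although it could equally improve if the centre proves dearer to run. Showing the return across the planned group sizes (4 and 6 against 8 and 12) would be informative but is optional.
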